**LIST OF ABBREVIATIONS AND RELEVANT DEFINITIONS**

|                |                                                                                                                                                                                                                                                                                                                                           |
|----------------|-------------------------------------------------------------------------------------------------------------------------------------------------------------------------------------------------------------------------------------------------------------------------------------------------------------------------------------------|
| ABR     | General Assessment and Registration form (ABR form), the application form that is required for submission to the accredited Ethics Committee; in Dutch: Algemeen Beoordelings- en Registratieformulier (ABR-formulier)                                                                                                                    |
| AE      | Adverse Event                                                                                                                                                                                                                                                                                                                             |
| CA      | Competent Authority                                                                                                                                                                                                                                                                                                                       |
| CCMO    | Central Committee on Research Involving Human Subjects; in Dutch: Centrale Commissie Mensgebonden Onderzoek                                                                                                                                                                                                                               |
| CV      | Curriculum Vitae                                                                                                                                                                                                                                                                                                                          |
| DSMB    | Data Safety Monitoring Board                                                                                                                                                                                                                                                                                                              |
| EOS     | Early-Onset Sepsis                                                                                                                                                                                                                                                                                                                        |
| EU      | European Union                                                                                                                                                                                                                                                                                                                            |
| EudraCT | European drug regulatory affairs Clinical Trials                                                                                                                                                                                                                                                                                          |
| GCP     | Good Clinical Practice                                                                                                                                                                                                                                                                                                                    |
| GDPR    | General Data Protection Regulation; in Dutch: Algemene Verordening Gegevensbescherming (AVG)                                                                                                                                                                                                                                              |
| IC      | Informed Consent                                                                                                                                                                                                                                                                                                                          |
| METC    | Medical Research Ethics Committee (MREC); in Dutch: Medisch Ethische ToetsingsCommissie (METC)                                                                                                                                                                                                                                            |
| NTR     | Netherlands Trial Register ( https://www.trialregister.nl/ )                                                                                                                                                                                                                                  |
| NVK     | Nederlandse Vereniging voor Kindergeneeskunde                                                                                                                                                                                                                                                                                             |
| (S)AE   | (Serious) Adverse Event                                                                                                                                                                                                                                                                                                                   |
| Sponsor | The sponsor is the party that commissions the organisation or performance of the research, for example a pharmaceutical company, academic hospital, scientific organisation or investigator. A party that provides funding for a study but does not commission it is not regarded as the sponsor, but referred to as a subsidising party. |
| UAVG    | Dutch Act on Implementation of the General Data Protection Regulation; in Dutch: Uitvoeringswet AVG                                                                                                                                                                                                                                       |
| WMO     | Medical Research Involving Human Subjects Act; in Dutch: Wet Medisch-wetenschappelijk Onderzoek met mensen                                                                                                                                                                                                                                |

## SUMMARY

**Rationale:** Newborns are at risk for early-onset, within 72 hours after birth, sepsis (EOS). The incidence of proven EOS is 0.5-2.0 per 1000 live births. For the Netherlands, based on 170,000 births per year, this means approximately 85-340 newborns. However, approximately 5% of late preterm and term newborns are given antibiotics in compliance with current Dutch guideline, which is equivalent to 8,500 newborns per year. An alternative is the CE certified EOS calculator application, which calculates an individual risk of EOS for each newborn with treatment advice.

**Objective:** To investigate whether the use of the EOS calculator safely reduces antibiotic exposure in newborns with suspected EOS compared to the current Dutch guidelines.

**Study design:** A cluster-randomized study design (randomization at hospital level) with 10 hospitals.

**Study population:** Newborns in the first 24 hours after birth, at a gestational age of  $\geq 34$  weeks, with at least one risk factor or symptom consistent with EOS.

**Intervention:** Randomization will take place at cluster level for either the EOS calculator or antibiotics administration according to the Dutch guideline.

**Main study parameters/endpoints:** *Co-primary superiority outcome:* The proportion of patients starting antibiotic therapy started for suspected and, or proven EOS in the first 24 hours after birth. *Co-primary non-inferiority outcome:* The presence of one or more of four predefined safety criteria, namely 1) the need for any respiratory support, and/or 2) the need for an intravascular fluid bolus for hemodynamic instability due to sepsis, and/or 3) referral to a Neonatal Intensive Care Unit for sepsis treatment, and/or 4) proven EOS.

*Secondary endpoints:* The total duration of antibiotic therapy; The percentage antibiotic therapy started for suspected and, or proven EOS if symptoms started between 24-72 hours after birth; Quality of life: To get an impression of the impact of (suspected) EOS on parents/guardians and their child, parents/guardians will be asked to fill in a questionnaire on day 14.

**Nature and extent of the burden and risks associated with participation, benefit, and group relatedness:** This study will have negligible risks and minimal burden.

**Burden:** -Newborns who receive antibiotic therapy: An intravenous cannula will be inserted for antibiotic treatment and blood sampling. A second blood sample by venipuncture will be collected after 24 hours. This is part of standard medical treatment. One questionnaire will be sent to the parents/guardians to fulfill on day 14, which is extra for this study. The questionnaire includes a minimum of 22 questions, which may expand up to 32 questions (since some questions are dependent of other questions). It will take about 10-15 minutes to complete. - Newborns who do not receive antibiotic therapy: No blood samples taken. Clinical observation for at least 12-24 hours. This is part of standard medical treatment. **Risks:** -The risks

associated with participation are very low because newborns will be closely observed when no antibiotics will be prescribed. **Benefits:** -More specific risk analysis. Not all subjects will benefit personally from study participation. When no antibiotics will be prescribed: no separation of mother and child, no painful procedures, and a shorter hospital stay (including fewer costs), and no unnecessary exposure to antibiotics. **Group relatedness:** This study can only be performed with this specific group of patients, as it will provide age-specific and risk factor-specific data that cannot be obtained otherwise.

## 1. INTRODUCTION AND RATIONALE

Newborns are at risk for early-onset sepsis (EOS) (1,2). A (suspected) EOS is defined as a (suspected) infection that develops within 72 hours after birth. The incidence of confirmed EOS is 0.5-2.0 per 1000 live births. For the Netherlands, this translates to approximately 85-340 EOS cases yearly.

Suspicion of EOS is often based by doctors on risk factors and nonspecific clinical symptoms, such as maternal fever during labor or rapid breathing in the newborn. The classic infection parameters in the blood of newborns are of little to no value to rule out an infection at the time of presentation (3). The combination of the difficulty to recognize EOS in time and the risk of serious consequences of EOS not treated timely has resulted in a low threshold for the start of empirical antibiotic treatment. This has led to significant overtreatment; it is estimated that in the Netherlands about 5% of all newborns receive antibiotic therapy for suspected EOS, equivalent to 8,500 newborns per year (4–6), compared to the estimated 85-340 of confirmed EOS cases. Adverse consequences of antibiotic overtreatment are increasingly recognized (4). In the short term, it leads to separation of parents and newborn, invasive painful procedures (with possible long-term consequences for brain development), and unnecessary hospitalization with associated costs. In the longer term, there are significant disadvantages for the microbiome and immune system, found to be associated with obesity (7), eczema, asthma (8,9), and diabetes later in life (10). In addition, at the population level, overuse of antibiotics leads to resistant infections that are difficult to treat.

The current standard of care is the NVK guideline "Prevention and treatment of early-onset neonatal infections" (11). The aim of this guideline is uniform, evidence-based, diagnosis and treatment of early-onset neonatal infections, including careful use of antibiotics. The NVK guideline is an adaptation of the 2012 version of the National Institute for Health and Care Excellence (NICE) guideline "Antibiotics for early-onset neonatal infection: antibiotics for the prevention and treatment of early-onset neonatal infection" (12).

The NVK guideline uses risk factors and symptoms to categorically indicate which newborns need antibiotics (11). Evaluating its use in 9 Dutch hospitals, we found limited adherence, especially when antibiotics are recommended by the guideline (13). This limited adherence indicates that it is desirable to amend the current guideline or that the use of an alternative method should be further investigated.

A new method for determining which newborns need antibiotics is the “EOS calculator” (14,15). Developed in the United States, this method uses a combination of detailed information about risk factors and the presence of specific symptoms to calculate an individual risk of EOS for each newborn. The EOS calculator is an algorithm that divides newborns into risk groups with concrete treatment advice (antibiotics, extra observation, normal care). The EOS calculator calculates the risk for an individual newborn using 5 maternal risk factors (gestational age, duration of rupture of membranes, highest intrapartum maternal temperature, use of intrapartum antibiotics, maternal Group B Streptococcus (GBS) colonization status) combined with the newborn’s clinical condition after birth. These data are objective and easy to retrieve, without additional actions.

The EOS calculator has been developed and validated using data of over 600,000 newborns born with a gestational age of 34 weeks or more. A subsequent large-scale implementation study included 204,485 newborns and showed a decrease in antibiotic use from 5.0% to 2.6% (16). EOS incidence and readmissions for EOS did not change after implementation, nor were any other adverse effects observed. The EOS calculator has now been evaluated in more than 20 studies, of which 8 with actual implementation. Meta-analysis shows up to an average of 44% less antibiotic use, without indications of negative consequences (17). Implementation in Tergooi hospital yielded comparable results (18). There are no known implementation studies in which EOS calculator use was not effective or proven unsafe.

For the Dutch situation, equipoise between the current guideline and the EOS calculator can be established given balance of risk for both over- and undertreatment of EOS for both strategies: the current guideline is likely to result in more overtreatment with adverse consequences, but potentially carries a smaller risk for treatment delay (although it is unclear to what clinical significance). A large body of evidence now supports the safety of the EOS calculator approach, but validation outside of the North-American setting is limited, especially for safety outcomes. Equipoise between both strategies is confirmed by the recently updated version of the NICE guideline (the NVK guideline was based on the 2012 version), which includes use of the ‘EOS calculator’, as a valid alternative approach to allocate antibiotics to newborns.(19) Equipoise can also be inferred from recommendations of the American Academy of Pediatrics, which considers both a risk-factor based approach and the EOS calculator as valid strategies. We compared the EOS calculator to the NVK guideline in a post-hoc analysis of our multicenter study (20), and found that the EOS calculator recommended significantly fewer antibiotics than the NVK guideline. This result is in line with the results of previous international research showing that the EOS calculator is proven to be effective and safe for reducing antibiotic overtreatment (17,21).

A prospective cluster-randomized Dutch validation study of the EOS calculator is needed before complete adoption of the EOS calculator, because of the following reasons:

1) Multicenter validation of actual EOS calculator use has not been performed in the Netherlands.

2) To date, no randomized prospective study of EOS calculator use with safety as an outcome measure has been performed. Specifically, there are no studies that take into account the potential effects of a treatment delay due to EOS calculator use. This especially holds true for cases that are clinically suspect for EOS, but not culture-confirmed. The study here proposed by us is, to the best of our knowledge, the first.

This protocol describes a cluster-randomized trial, which is the logical next step to our previous research (18,22–28). The study aims to investigate whether the use of the EOS calculator safely reduces antibiotic exposure in newborns with suspected EOS compared to the current Dutch guideline.

## 2. OBJECTIVES

The primary objectives of this study are:

1. To investigate whether the use of the EOS calculator safely reduces antibiotic exposure in newborns with suspected EOS in the first 24 hours after birth.
2. To investigate the presence of one or more of the following four predefined safety criteria, namely 1) the need for any respiratory support, and/or 2) the need for an intravascular fluid bolus for hemodynamic instability due to sepsis, and/or 3) referral to a Neonatal Intensive Care Unit for sepsis treatment, and/or 4) proven EOS.

Secondary objectives of the study are:

1. To investigate if the use of the EOS calculator decreases the total duration of antibiotic therapy in newborns with suspected EOS.
2. To investigate if the use of the EOS calculator decreases the percentage of antibiotic therapy started for suspected and, or proven EOS if symptoms started between 24-72 hours after birth.
3. To study the impact of (suspected) EOS on parents/guardians.

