In order to meet requirements of the European Regulations for Medical Devices, the EOS calculator has been developed as a smartphone application specifically for this study, and CE marking has successfully been obtained (see chapter 5). Only in the five hospitals randomized for the EOS calculator this application will be available for all physicians who have a treatment relationship with newborns at risk for EOS.

**Equality:** We use the same strategy to include and observe participating newborns to ensure that the control group and the intervention group are equally recruited and monitored. Each newborn in participating hospitals is evaluated for elevated EOS risk. In case one or more criteria for elevated maternal EOS risk or neonatal clinical signs of EOS are met (in accordance with the NVK guideline, Table 1), clinical evaluation of the newborn by a pediatric resident or pediatrician will take place within 4 hours after birth. After concluding eligibility, the advice of either the NVK guideline or the EOS calculator (depending on randomization) to observe or to start antibiotic therapy is followed. We maintain an observation period of at least 12-24 hours for the NVK guideline-group and at least 24 hours for the EOS calculator-group. These observation periods are in accordance with the advice of both guidelines. Observation in both groups will consist of controls of vital parameters (heart rate, respiratory rate, and temperature) every 3 hours by the nurse, and a minimum of two physical examinations (within 4 hours after birth and before discharge) by the physician.

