### 4.2 Inclusion criteria

In order to be eligible to participate in this study, a subject must meet all of the following criteria:

- postmenstrual age of 34 weeks or more;
- age between 0-24 hours;
- at least one EOS risk factor or clinical sign of infection (suspected of EOS) present within the first 24 hours of life (Table 1);
- parental/guardian consent.

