#### 6.1.2 Secondary study parameters/endpoints

- The total duration of antibiotic therapy.
- The proportion of antibiotic therapy started for suspected and, or proven EOS if symptoms started between 24-72 hours after birth.

- Quality of life: To get an impression of the impact of (suspected) early-onset sepsis on the quality of life (QoL) of both parents/guardians and their child, parents/guardians will be asked to fill in a questionnaire on day 14 after birth. Our questionnaire is based on (parts of) two questionnaires, which were used in different studies assessing the effect of early intravenous-to-oral antibiotic switch (30), and the influence of resiliency and stress on parental/guardian perspective of the future QoL of their newborns (31). The first part collects information on medical factors after hospitalization (side effects, number of medical visits, readmission, and medication use) and basic needs of the newborn (sleep quality of the patient, (breast)feeding success rate). The second part addresses the subjective parental/guardian evaluation of the impact of newborns' admission, and parental/guardian projection of future QoL of their newborn. The last part of the questionnaire collects demographic data. We hypothesize that the maternity period is experienced more positive if mother and child go home quickly, because of less hinder to take care of their child (for example, earlier initiation of breastfeeding), and less stress (for example, emotionally or financially). The questionnaire is designed in close collaboration with Care4Neo. Care4Neo (formerly Association of Parents of Incubator Children) represents the interests of parents/guardians whose child is admitted to a hospital immediately after birth.

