## **6.3 Study procedures**

For all included newborns, maternal and neonatal data on risk factors will be collected. The newborn's date and time of birth will be collected because the most important collected parameters are time dependent and need these date and time of birth as a reference. Physical examinations of the newborn will be performed at least twice (at birth and before discharge), and more often if necessary (depending on clinical findings). Finally, for

participating newborns, a single (online) questionnaire will be sent (via Castor EDC) to the parents/guardians to fulfill on day 14 after birth. The questionnaire includes a minimum of 22 questions, which may expand up to 32 questions (since some questions are dependent of other questions). It will take about 10-15 minutes to complete.

For newborns without antibiotic therapy, clinical observation for at least 12-24 hours will be performed: vital parameters (heart rate, respiratory rate, and temperature) will be measured 1, 3, 6, 9, 12, 15, 18, 21 and 24 hours after birth. This is part of standard medical treatment. Data on physical examinations will be collected. Data on readmission for suspected or proven EOS will be collected.

For newborns with intravenous antibiotic therapy, two blood samples will be taken: during insertion of the intravenous cannula before starting antibiotics (blood culture; blood cell count, CRP), and approximately 24-36 hours after the start of antibiotics by capillary or vena puncture (CRP). This is part of standard medical treatment. Duration of hospital stay will be at least 24-36 hours, could be extended depending on the clinical condition and blood culture results and non-EOS factors. During admission the need for any kind of respiratory support and the need for intravascular fluid administration will be recorded daily. Referral to a neonatal intensive care unit (NICU) will be recorded and relevant clinical data during NICU admission will be obtained by the main investigator or the research nurse/assistant of the participating hospital. Data on sort and duration of antibiotic therapy and blood culture results will be collected.

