#### 8.2.1 Quality of life

To get an impression of the impact of (suspected) early-onset sepsis on the quality of life (QoL) of both parents/guardians and their child, parents/guardians will be asked to fill in a questionnaire on day 14. See also 6.1.2. Outcome reporting will be mainly descriptive. Mixed models can be used to further explore the effect of treatment and center if a trend is observed for some of the questions. Mean scores and standard deviations are calculated for composite indicators. We use t-tests to evaluate differences in mean scores between groups for normally distributed data. The significance level is set at an alpha value of  $<.05$ .

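### Secondary objective 3, its hypothesis and its analysis do not point to the same contrast, and none of them is tied to the randomised arms

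*Protocol*

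**What the plan says.** - **Objective (section 2).** Secondary objectives 1 and 2 both ask what use of the EOS calculator does. Objective 3 reads "To study the impact of (suspected) EOS on parents/guardians".
- **Who is enrolled (section 4.2).** Every participant must have "at least one EOS risk factor or clinical sign of infection (suspected of EOS) present within the first 24 hours of life".
- **Who is asked (section 6.3).** The questionnaire goes to families of participants only: "participating newborns, a single (online) questionnaire will be sent (via Castor EDC) to the parents/guardians to fulfill on day 14 after birth".
- **Hypothesis (section 6.1.2).** "We hypothesize that the maternity period is experienced more positive if mother and child go home quickly", explained by easier care of the child and less stress.
- **Analysis (section 8.2.1).** "Outcome reporting will be mainly descriptive". Mixed models are optional and depend on a trend being seen in some questions. Then: "We use t-tests to evaluate differences in mean scores between groups for normally distributed data", at a 5% significance level.
- **General rule (section 8.2).** Continuous secondary outcomes are to be analysed with a linear mixed model that estimates mean differences, with random intercepts and slopes as appropriate.

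**The concern.** The three places that should define one question define different ones. The objective asks about a condition that all participants share. The hypothesis sorts families by a variable that arises after allocation. The analysis compares groups that it does not define, by a test that takes no account of the hospital as the unit of randomisation.

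Two unsound results are therefore open to an analyst who follows the text. One compares early with late discharge, which largely sets parents of well newborns against parents of treated or ill newborns and could favour early discharge whatever the calculator does. Sections 9.4 and the Summary already list a shorter stay as a benefit when antibiotics are withheld, so such a result could be taken as a parental benefit of the strategy. The other is a t-test by arm whose p-value is too small because patients within a hospital are treated as independent. The question that the trial can answer with the protection of randomisation, whether parents' reports differ between calculator and guideline hospitals, is not stated as the objective.

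**Working it through.** The protocol gives no figure for this endpoint, so there is none to reproduce. The check is mainly a comparison of sections, with one illustrative calculation.

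**1. Contrast implied by each section**

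| Place | Contrast |
|---|---|
| Section 2, objective 3 | None named |
| Section 6.1.2, hypothesis | Quick versus slow return home |
| Section 8.2.1, mixed model | Treatment and center, only if a trend is seen; treatment could mean the assigned strategy or antibiotics |
| Section 8.2.1, t-test | Groups, not defined |
| Section 8.2, continuous secondary outcomes | Mean difference from a linear mixed model |

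**2. Can objective 3 be read as an effect?** All participants have suspected EOS by the inclusion criteria, only their families are surveyed, and they are surveyed once. There is no unexposed group and no baseline. The effect of suspected EOS cannot be estimated in this trial. A description of these parents' experience can be given.

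**3. Is time to discharge a sound contrast?** Section 3 says that discharge of treated newborns depends on treatment duration and clinical course. Section 6.3 says that their stay "could be extended depending on the clinical condition and blood culture results and non-EOS factors". Discharge time is thus driven by illness and fixed after allocation, so a comparison by it is confounded.

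**4. Can discharge time stand in for the arm?** Two stated features pull in opposite directions. Section 4.4 expects fewer treated newborns with the calculator (25% against 40%), which would shorten the average stay. Section 3 sets the minimum observation the other way: "We maintain an observation period of at least 12-24 hours for the NVK guideline-group and at least 24 hours for the EOS calculator-group". The stated minimum times do not determine which arm has the shorter stay.

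**5. Effect of ignoring hospitals in a t-test by arm**

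Inputs: 183 participants per hospital and ICC 0.0025 (section 4.4). Assumptions: that ICC, given for the primary outcomes, also applies to the questionnaire scores; all families respond; hospitals are of equal size.

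Design effect = 1 + (m − 1) × ICC

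- m = 183, ICC 0.0025: 1 + 182 × 0.0025 = 1.455, about 1.46. The true standard error is √1.455 = 1.21 times the one that the t-test uses.
- m = 164 (the section 4.4 cluster size before the drop-out allowance): 1 + 163 × 0.0025 = 1.41.
- Range in the unknown ICC at m = 183: ICC 0 gives 1.00; twice the plan's value, 0.005, gives 1 + 182 × 0.005 = 1.91.

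In a normal approximation, a nominal two-sided 5% test at design effect 1.455 has an actual error rate of 2 × [1 − Φ(1.96/1.206)] = 2 × [1 − Φ(1.625)], about 10%.

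**The case against.** The strongest reply is that this is a descriptive endpoint. Sections 6.1.2 and 8.2.1 speak of gaining an impression, and describing what parents go through is a legitimate aim that needs no unexposed group. Elsewhere the protocol uses control group and intervention group for the randomised arms, so that is the natural reading of the undefined groups. Section 8.2.1 does mention the effect of treatment, and section 8.2 already supplies a mixed model. Primary objective 2 also names no comparator, yet section 8.1 analyses it by arm. Definitions of this kind are often left to the statistical analysis plan.

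Much of this stands, and it sets the limits of the point:

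- A reader might infer that objective 3 has no valid comparator at all. The protocol does not support that: both arms receive the same questionnaire, and an arm comparison is at least alluded to.
- A reader might infer that an early-versus-late discharge analysis is planned. No section specifies one, and the section 6.1.2 sentence can be read as the reason why fewer antibiotics might help families.
- A reader might try to put a size on the confounding, or on the difference in stay between arms. The protocol does not give the figures for either. In particular, it does not say how the safety events divide between treated and untreated newborns, and section 6.1.1 notes that they overlap with causes other than EOS.

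What the reply does not remove is that section 8.2.1 goes beyond description. It sets a significance test at 5%, chooses a method that ignores clustering although section 8.2 provides one that does not, and makes the better model depend on first seeing a trend. These are choices the protocol states, not details it leaves open.

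**Conclusion.** The point holds at low severity. Objective, hypothesis and analysis for the parent-reported endpoint do not describe one contrast, and the randomised comparison that the data can support is not tied to any of them. Followed literally, the text allows a comparison confounded by illness or a t-test that ignores the hospital.

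The size of the second problem is illustrative: a design effect of about 1.46, resting on the assumption that the plan's ICC of 0.0025 carries over to these scores with full response. It would be smaller with fewer responses or a lower ICC, and larger with a higher ICC. The first problem cannot be sized from the protocol. No primary conclusion, sample size or data collection is affected.

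**What to change.** 1. Reword secondary objective 3 and the section 6.1.2 hypothesis as a comparison of day-14 parent/guardian-reported scores between hospitals assigned to the EOS calculator and hospitals assigned to the NVK guideline. A descriptive account of parents' experience can stay beside it.
2. In section 8.2.1, define the groups as the randomised arms. For the composite scores, replace both the t-test and the trend condition with the linear mixed model of section 8.2.
3. Label any comparison by antibiotic receipt or time to discharge as descriptive and confounded, and not as evidence for the calculator.

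The cost is a few sentences in the protocol or the statistical analysis plan. It needs no new patients, procedures or data.
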